#### Subgroup analyses

The following patient categories will be included in all primary and secondary analyses but will also be analysed separately as subgroup analyses:Patients with known pre-existing coagulopathyOral anticoagulant therapy (except for aspirin)Excluding patients with severe traumatic brain injury (AIS brain 4,5 or 6)Patients who arriving in a coagulopathic state (PTr > 1.2)Patients who received a massive transfusion (10 or more RBC units in the first 24 h)

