### Statistical considerations

#### Sample size

Based upon legacy registry data from the partners, approximately 28% of patients will need massive transfusion or die. It is expected that this figure will decrease to an overall proportion of 15% in the VHA group (i.e. using VHA-guided strategy). In order to detect a difference from 28% to 15% with a power of 80% and a two-sided alpha of 0.05, 170 patients per group are required. One hundred and ninety-six patients per study arm allows a 13% dropout rate, with an allocation ratio of 1. The planned sample size for this study is 392 patients for which MTP is activated and transfusions initiated, 196 in each study arm.

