#### Method of analysis

All primary and secondary outcomes will be analysed as intention-to-treat, and will include all randomised patients for whom the primary outcome of ‘alive’ and ‘free of massive transfusion’ at 24 h is recorded. The primary endpoint of patients who are alive and free of massive transfusion at 24 h will be assessed by difference in proportion with 95% confidence intervals. The chi-square test or Fischer’s exact test will be used were appropriate. Absolute risk reduction and relative risk reduction by VHA-guided therapy will be calculated.

Kaplan-Meier mortality estimates between the two arms for all-cause mortality at 6 and 24 h, as well as 28 and 90 days post admission, will be estimated for the secondary endpoint of death.

A per-protocol analysis and a sensitivity analysis will be performed for the primary endpoint. The following patients will be excluded from the per-protocol analysis:Patients who do not have at least one ROTEM®/TEG®/CCT test performed *and*
Who die within 60 min after baseline blood sampling *or*
Who achieve haemostasis within 60 min of baseline sampling

Both ROTEM®-guided and TEG®-guided therapy together (i.e. the VHA arm) will be compared with the CCT arm. Separate analyses will be performed for ROTEM®-guided and TEG®-guided therapy alone for primary endpoints and correction of coagulopathy.

All applied tests will be two-sided and *p* values of 0.05 will be accepted as statistically significant. We will report *p* values with and without correction for multiple testing.

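### Subgroups are to be analysed separately under a general 0.05 rule, which cannot show whether the VHA effect differs between subgroups

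*Protocol article*

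**What the plan says.** The Subgroup analyses section opens: "The following patient categories will be included in all primary and secondary analyses". It then says that these categories "will also be analysed separately as subgroup analyses". As printed there are five:

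- known pre-existing coagulopathy
- oral anticoagulant therapy other than aspirin
- the population without severe traumatic brain injury
- arrival with PTr above 1.2
- a last category worded "Patients who received a massive transfusion (10 or more RBC units in the first 24 h"

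The section does not name the endpoints for the separate analyses, and it does not call them exploratory.

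The Method of analysis section sets a rule for every test: "All applied tests will be two-sided", and p "values of 0.05 will be accepted as statistically significant". It adds that the report will give p "values with and without correction for multiple testing". It does not say which correction is meant, which tests form the family, or which set of p values decides. The subgroup tests are not exempted from the general rule.

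**The concern.** The baseline subgroups ask who benefits. The Background makes this a live question: the hypothesis is that VHA works by targeted correction of coagulopathy, yet it also expects savings in patients without coagulopathy. Whether the effect differs between patients who arrive coagulopathic and those who do not is a question about the difference between two effects. A p value from the coagulopathic patients alone does not address it. A significant result in one stratum beside a non-significant one in another does not address it either, because the two can easily diverge when the effects are identical.

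The Discussion says that the trial is meant to inform guidelines for massive transfusion, so a misread subgroup result could influence practice.

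**Working it through.** **Inputs.** From the Sample size section: "approximately 28% of patients will need massive transfusion or die", falling to 15% with VHA; 80% power; two-sided alpha 0.05; 170 evaluable per arm; 196 per arm after 13% dropout. The article gives no subgroup sizes, so the share f of patients in a subgroup is an assumption, varied from 10% to 70%.

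**1. The plan's own figure.** The two-proportion formula with pooled variance gives 156 per arm for 28% vs 15%. With continuity correction it gives 171, which agrees with the stated 170 to within rounding. 170 / (1 − 0.13) = 195.4, rounded up to 196. The sample size reproduces. The power figures below use the uncorrected test, under which 170 per arm has 83% power.

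**2. Same true effect everywhere: how often do separate tests disagree?** With n = 170f per arm in the subgroup and mean proportion (0.28 + 0.15)/2 = 0.215:

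- SE under the null: SE0 = √(2 × 0.215 × 0.785 / n)
- SE under the alternative: SE1 = √((0.28 × 0.72 + 0.15 × 0.85) / n)
- Power = Φ((0.13 − 1.96 × SE0) / SE1)

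The subgroup (power p) and its complement (power q) contain different patients. The chance that exactly one is significant is therefore p(1 − q) + q(1 − p).

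Example, f = 0.1. In the subgroup n = 17, SE0 = 0.1409 and SE1 = 0.1391, so p = Φ(−1.05) = 14.7%. In the complement n = 153 and q = 79.3%. Disagreement = 0.147 × 0.207 + 0.793 × 0.853 = 71%.

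| Assumed share f | Power in subgroup | Power in complement | Chance of disagreement |
|---|---|---|---|
| 0.1 | 14.7% | 79.3% | 71% |
| 0.3 | 35.7% | 68.7% | 55% |
| 0.5 | 54.2% | 54.2% | 50% |
| 0.7 | 68.7% | 35.7% | 55% |

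There is no difference in effect in any row.

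**3. No effect anywhere: false positives.** For k independent, uncorrected tests at 0.05 on the primary endpoint, the chance of at least one is 1 − 0.95^k. This gives 18.5% for the four baseline categories and 22.6% for all five. The categories overlap, so the tests are not independent and these figures are illustrative.

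**4. What the interaction test can deliver.** Take an effect of 28% vs 15% in the subgroup and none (28% vs 28%) outside it, on the risk-difference scale:

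V = (0.28 × 0.72 + 0.15 × 0.85) / (170f) + (2 × 0.28 × 0.72) / (170(1 − f)); power = Φ(0.13/√V − 1.96).

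At f = 0.5, V = 0.3291/85 + 0.4032/85 = 0.00862, √V = 0.0928, and power = Φ(1.40 − 1.96) = 29%. The other shares give 14% (f = 0.1), 26% (f = 0.3) and 24% (f = 0.7).

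**5. The massive-transfusion category.** Success on the primary endpoint requires fewer than 10 RBC units at 24 h. Every patient in this category received 10 or more, so every one has failed, and the comparison is 0% vs 0% success. Membership is also determined after randomisation and may itself be affected by treatment, so other comparisons within the category are not protected by randomisation.

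**The case against.** The best defence is that interaction terms, forest plots and exploratory labels usually belong in an analysis plan, which is not shown, and that separate analysis does not rule out an interaction test. This stands as far as silence goes: the mere absence of an interaction test would not be a finding. However, the article does state a method, and the point rests on that choice.

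Three stronger readings are tempting, and the text does not support them.

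- **Every endpoint is tested in every subgroup.** The phrase about all primary and secondary analyses says that these patients stay in the main analyses. The endpoints for the separate analyses are unstated. Multiplying subgroups by secondary endpoints, which would make a false positive almost certain, has no basis in the text.
- **Nothing is corrected for multiplicity.** Corrected p values are promised too. If a standard correction covered these tests, the error rate in step 3 would come down. Correction does not meet the main point, because a corrected within-subgroup p value still does not test a difference in effect.
- **The subgroups are all small, or the trial plans to make subgroup claims.** No sizes are given, and the population without severe brain injury could be large. The article announces no such claim. Misreading is a risk, not a stated intention.

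It is also fair to object that the interaction test has low power itself. That is correct. It is a reason to treat the results as exploratory, not a reason to keep a method that answers a different question.

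**Conclusion.** The point holds in a limited form. Separate within-subgroup tests under the 0.05 rule, corrected or not, cannot establish who benefits from VHA guidance. With one common effect, a subgroup and its complement would disagree on significance in about 50% to 71% of trials. This rests on 170 evaluable per arm, the plan's 28% vs 15%, and assumed shares of 10% to 70%. The false-positive chance of up to 18.5% applies only to four uncorrected, independent tests of the primary endpoint. The massive-transfusion category is a separate fault: its primary-endpoint comparison carries no information, and an interaction test would not cure that. The main primary analysis is not affected.

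**What to change.** For the primary endpoint, and only for the subgroups defined at baseline (pre-existing coagulopathy, oral anticoagulant therapy, severe traumatic brain injury yes or no, arrival PTr above 1.2):

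- fit a model in all randomised patients with a treatment-by-subgroup term for each factor;
- report the interaction estimate with its 95% CI, and the effect estimates within subgroups with their CIs;
- base no claim on within-subgroup p values, and label the results exploratory.

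Do not use the massive-transfusion category as a subgroup for the primary endpoint.

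The change costs a few sentences and uses data already collected. The downside is the low interaction power, about 14% to 29% under the assumed shares if the effect is confined to the subgroup. The text should therefore also say that a non-significant interaction does not show a uniform effect.

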### Inclusion criteria

Adult trauma patients (according to local definitions) will be enrolled if they present with clinical signs of haemorrhagic shock, according to the responsible trauma team leader, activate the local massive haemorrhage protocol, according to the participating institutions’ specific routines, and initiate first transfusion. Participants must be randomised within 3 h of injury and 1 h of admission to the ED of the participating study site. Agreement is provided on behalf of incapacitated patients by a personal consultee (PC) or a nominated consultee (NC).

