### Primary endpoint

The primary endpoint is the proportion of subjects alive and free of massive transfusion (less than 10 units of RBC transfused) at 24 h post admission.

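### The massive-transfusion subgroup is defined by failure of the primary endpoint, so its primary comparison is empty and its secondary comparisons are open to selection bias

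*Protocol article*

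**What the plan says.** The Primary endpoint section of the protocol article defines success as being "alive and free of massive transfusion (less than 10 units of RBC transfused) at 24 h post admission".

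The Subgroup analyses section opens with "The following patient categories will be included in all primary and secondary analyses but will also be analysed separately as subgroup analyses". The last of its five categories is "Patients who received a massive transfusion (10 or more RBC units in the first 24 h". The other four are pre-injury or injury characteristics, or status on arrival. The section does not limit the last category to particular outcomes or to descriptive reporting.

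Three other statements bear on the point:

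- On timing, the Inclusion criteria section states: "Participants must be randomised within 3 h of injury and 1 h of admission to the ED of the participating study site". It also requires that a first transfusion has been started.
- On the expected effect, the Background section gives the hypothesis that VHA guidance will reduce the amount of blood products given. The Sample size section assumes that "approximately 28% of patients will need massive transfusion or die" and adds: "It is expected that this figure will decrease to an overall proportion of 15% in the VHA group".
- On the main analysis, the Method of analysis section specifies intention-to-treat for all primary and secondary outcomes.

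**The concern.** A subgroup analysis supports a randomised comparison when membership is fixed before allocation or cannot be influenced by it. This category is defined by an outcome. That raises two separate problems.

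First, the category is one of the two ways of failing the primary endpoint, so the primary endpoint cannot vary within it.

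Second, if VHA guidance works as hypothesised, fewer VHA than CCT patients reach 10 units, and those who do are a different selection of patients. A difference in mortality, organ dysfunction or length of stay between the arms of this subgroup would then mix any treatment effect with a difference in who got in. Patients who die before receiving 10 units cannot enter at all, which adds selection by survival. Red cell use over 24 h, a secondary endpoint, is also restricted to 10 units or more in every member.

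What is at stake is a pre-specified result on mortality among the heaviest bleeders that readers could take as a valid treatment comparison.

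**Working it through.** **1. The two definitions side by side.** Let R be the red cell units received by 24 h.

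- Success: alive at 24 h and R < 10.
- Subgroup: R ≥ 10.

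No patient satisfies both, so P(success | subgroup) = 0 in each arm. The risk difference is 0 − 0 = 0, the relative risk of failure is 1/1 = 1, and the relative risk of success is 0/0, which is undefined. No chi-square or Fisher test carries information. This takes both 24 h windows to start at admission. The endpoint says so; the subgroup line says only the first 24 h, and admission is the natural reading.

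**2. Timing.** Randomisation comes at most 1 h after admission, so at least 24 − 1 = 23 h of the window follows it. Because a first transfusion must already have started, some units may precede allocation. Membership is therefore mostly, not wholly, determined after randomisation.

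**3. Does the trial expect treatment to change membership?** The design rates are 28% (CCT) and 15% (VHA) for massive transfusion or death. The plan states "with a power of 80% and a two-sided alpha of 0.05, 170 patients per group are required". For two proportions with 80% power and two-sided alpha 0.05, I get 171 per group with a continuity correction (156 without), which agrees with the stated 170 to within rounding. Allowing 13% dropout, 170/0.87 = 195.4, rounded up to 196 per arm, as stated. The design figures are not in question.

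Expected failures per arm are 196 × 0.28 = 54.9 (CCT) and 196 × 0.15 = 29.4 (VHA). The documents do not say what share of failures are massive transfusions. If that share is between 40% and 100% and equal in both arms (an assumption), the subgroup holds about 22 to 55 CCT patients and 12 to 29 VHA patients. Under the plan's own hypothesis the two arms of the subgroup differ in size, so they are not selected alike.

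**4. How large could the bias be?** This is an illustration with assumed inputs:

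- Massive transfusion is the same share s of failures in both arms, so it falls in the ratio 28 to 15.
- VHA brings nobody to 10 units who would not have reached it under CCT.
- Mortality, read at a later time such as 28 days, is 30% among CCT massive-transfusion patients.
- Averted cases would have had mortality m, and VHA changes the survival of none of the patients counted here.

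Apparent VHA subgroup mortality = (0.28s × 0.30 − 0.13s × m) / (0.15s). The share s cancels, leaving (0.084 − 0.13m)/0.15.

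| m (assumed) | 0.084 − 0.13m | VHA subgroup mortality | Difference from CCT 30% |
|---|---|---|---|
| 15% | 0.0645 | 43% | +13 points |
| 20% | 0.0580 | 39% | +9 points |
| 25% | 0.0515 | 34% | +4 points |
| 30% | 0.0450 | 30% | 0 |
| 35% | 0.0385 | 26% | −4 points |

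**5. A second illustration.** Let severity be standard normal, let patients above an arm-specific cut-off receive massive transfusion, and let death depend on severity alone (log-odds −1.5 plus a slope of 0.5 to 1.5 per standard deviation). With shares of 40% to 100%, the VHA subgroup shows about 3 to 12 points more deaths, although treatment has no effect on death. The direction is built in here, because this model always averts the least severe cases.

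**The case against.** The best defence is that this is an additional analysis. These patients stay in all primary and secondary analyses, and the primary estimate, the sample size and the intention-to-treat secondary results do not depend on the subgroup. It is one of five, and the article rests no conclusion on it. An empty 0% versus 0% result would be obvious to any analyst. The article also does not spell out which outcomes will be compared by arm in this category; that may be left to a fuller document. All of this stands as a limit on severity. It does not rescue the listing: the article fixes the category itself, places it beside genuine baseline subgroups, and says nothing that confines it to description.

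Three stronger readings are tempting, and the documents support none of them:

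- A reader might infer that membership counts only units given after randomised care begins. The endpoint window runs from admission, and some units can come earlier.
- A reader might infer a predicted 13-point false harm. That is one row of an assumed table. The 28% and 15% are rates of massive transfusion or death combined, so they fix the massive-transfusion rates only under the equal-share assumption. Changing the mortality of averted cases changes the size and then the sign.
- A reader might infer that the trial's main conclusion is compromised. It is not.

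**Conclusion.** The point holds in two parts of different strength. The empty primary comparison follows from the definitions alone, given that both windows start at admission. The exposure of secondary comparisons to selection bias follows from membership being mostly post-randomisation and being something the trial expects VHA guidance to alter. It would disappear only if treatment did not affect who is massively transfused, or if the averted cases happened to carry the same risk as the rest.

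Neither the size nor the direction of that bias can be derived from the documents. The assumed range of +13 to −4 percentage points in apparent mortality shows that such a comparison could mislead either way with no true effect on death. It is not an estimate of what the trial will find. Because the intention-to-treat analyses are untouched, this is a correction that should be made, not a fault that undermines the trial.

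**What to change.** Either of two changes is sufficient:

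- delete this category from the Subgroup analyses section; or
- keep it as a descriptive table of massively transfused patients, stating that no test or effect estimate between arms will be given.

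If the aim is to learn about severe bleeders, define them by a characteristic fixed before randomisation that the trial already collects, and report an arm-by-subgroup interaction. The subgroup with PTr above 1.2 on arrival is already listed, but it measures coagulopathy and not bleeding volume. The article text does not name a baseline measure of bleeding severity, so the sponsor would need to check what the case report form holds.

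The cost is one line of wording and at most one fewer analysis. No new data are needed and no sample-size figure changes. It should be done before outcomes are analysed by arm.

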#### Sensitivity analyses

Missing data are not expected for the primary outcome. Sensitivity analysis for secondary outcomes will be assessed using 100 multiple imputations for missing data. Rubin rules will be used to summarise the results of the multiple imputations.

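### Every analysis, mortality included, is limited to patients with a recorded 24 h composite, and the planned imputation leaves out the primary endpoint

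*Protocol article*

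**What the plan says.** All references are to the protocol article.

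- *Method of analysis* sets the population: "All primary and secondary outcomes will be analysed as intention-to-treat, and will include all randomised patients for whom the primary outcome of" survival without massive transfusion at 24 h has been recorded. The rule names secondary outcomes explicitly, and *Secondary endpoints* lists all-cause mortality at 6 h, 24 h, 28 days and 90 days among them.
- The same section adds: "A per-protocol analysis and a sensitivity analysis will be performed for the primary endpoint". It then lists the per-protocol exclusions but does not describe the sensitivity analysis.
- *Sensitivity analyses* reads: "Missing data are not expected for the primary outcome. Sensitivity analysis for secondary outcomes will be assessed using 100 multiple imputations", with results combined by Rubin's rules.
- *Sample size* reads: "One hundred and ninety-six patients per study arm allows a 13% dropout rate, with an allocation ratio of 1". It does not say what kind of dropout is meant.
- *Subject withdrawal* permits withdrawal after randomisation, for example for ineligibility found in retrospect or for a major protocol deviation. *Data collection and follow-up for withdrawn subjects* keeps these patients under safety assessment to day 28, and *Subject replacement* replaces them.
- *Randomisation procedure* states that clinical staff and site investigators know the allocation.

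**The concern.** Whether the 24 h composite gets recorded is settled after randomisation. Making it a condition of entry to every analysis is a complete-case selection, even though the text calls it intention-to-treat. Because the people delivering care and deciding on withdrawals know the arm, the losses could differ between arms in number or in prognosis.

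The condition does most damage to mortality. Vital status can be known when the composite is not: a patient may have an incomplete red cell count, or may have been withdrawn and followed for safety to day 28. Such a patient has usable mortality data, and the rule discards them. The imputation of secondary outcomes does not help, because it works within a set from which the patient has already been removed.

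The second part concerns the primary endpoint. Imputation is confined to secondary outcomes on the strength of a forecast that primary data will be complete. If the forecast fails, the article names a sensitivity analysis for the primary endpoint but gives it no missing-data content.

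**Working it through.** **1. The plan's own figures.** Inputs from *Sample size*: "approximately 28% of patients will need massive transfusion or die"; "this figure will decrease to an overall proportion of 15% in the VHA group"; "with a power of 80% and a two-sided alpha of 0.05, 170 patients per group are required".

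- The usual two-proportion formula with pooled variance under the null gives 156 per group. With continuity correction it gives 171, against 170 stated, so the figure reproduces to within one patient.
- Dropout: 170 / (1 − 0.13) = 195.4, rounded up to 196 per arm and 392 in total, as stated.
- Allowance: 196 − 170 = 26 per arm, and 26 / 196 = 13.3%.

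The sample-size arithmetic is sound.

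**2. Who is removed by the entry condition.** The composite in *Primary endpoint* requires both survival and fewer than 10 red cell units at 24 h.

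| Information on record at 24 h | Composite | In the mortality analyses? |
|---|---|---|
| Death by 24 h | failure, whatever the count | yes, on a natural reading |
| 10 or more units | failure, whatever else is missing | yes, on a natural reading |
| Alive, complete count below 10 | success | yes |
| Alive, fewer than 10 units documented, count incomplete | undetermined | no, although 24 h status is known |
| Status at 24 h not captured, fewer than 10 units documented | undetermined | no, even if a later safety assessment establishes status |

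The last two rows are the patients at issue.

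**3. Sensitivity of the primary result.** The document gives no expected proportion missing, so the range below is an assumption. Let m patients per arm be missing out of 196, with failure of 28% (CCT) and 15% (VHA) among the rest. The observed difference is 13 points.

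- Worst case for VHA (all missing VHA patients fail, no missing CCT patients do): [0.13 × (196 − m) − m] / 196
- Best case for VHA (the reverse): [0.13 × (196 − m) + m] / 196

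| Missing per arm | Worst | Best |
|---|---|---|
| 2 (1%) | 11.8 points | 13.9 points |
| 4 (2%) | 10.7 | 14.8 |
| 6 (3%) | 9.5 | 15.7 |
| 10 (5%) | 7.2 | 17.4 |
| 26 (13.3%, the whole allowance) | −2.0 | 24.5 |

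For m = 4: 0.13 × 192 = 24.96, so (24.96 − 4) / 196 = 10.7% and (24.96 + 4) / 196 = 14.8%.

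**4. Where significance is lost in the worst case.** Failures are rounded to whole patients, with a pooled two-sample z.

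- m = 8: 53/196 v (28 + 8)/196, a difference of 8.7 points, z = 2.05.
- m = 9: 52/196 v (28 + 9)/196, a difference of 7.7 points, z = 1.81.

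The two-sided 5% threshold of 1.96 is crossed at 9 per arm, and 9 / 196 = 4.6%.

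**The case against.** The best defence is that the outcome is measured 24 h after admission in bleeding in-patients, and that the article has the timing and number of every blood product recorded. Near-complete primary data is a reasonable expectation, and the patients removed by the entry condition may be very few. This stands, and it limits the size of the point.

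Four stronger readings are tempting, and the document does not support them.

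- A reader might infer that the plan contradicts itself by budgeting 13% dropout while declaring that nothing will be missing. The text says only that missing primary data are not expected, and the 13% may cover withdrawn agreement or retrospective exclusion rather than an unobserved 24 h outcome. What remains is that the article does not say what the 13% covers. Since withdrawn patients are also replaced, those losses may be provided for twice.
- A reader might infer that the primary endpoint has no sensitivity analysis. One is promised, and its detail may properly sit in the full protocol or analysis plan. What remains is that the section on missing data confines imputation to secondary outcomes.
- A reader might infer that early deaths with an incomplete red cell count go unscored. The endpoint definition settles these as failures; an explicit sentence would only remove doubt.
- A reader might infer that missing data could erase the planned effect. The figure of −2.0 points is arithmetically right, but it needs the whole allowance to be missing outcome data, with opposite extremes in the two arms. It is a bound and not a forecast.

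None of this touches the analysis-set sentence. It is a stated rule rather than an omitted detail, and it applies to mortality as written.

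**Conclusion.** The point holds in a limited form. As written, the intention-to-treat set is conditional on a post-randomisation variable, and it excludes from all four mortality time points some patients whose vital status may be known. The planned imputation cannot restore them, and it does not reach the primary endpoint.

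The size depends on a proportion that the article does not give. At 1 to 2% missing per arm, the extreme-case bounds stay within about 10.7 to 14.8 points and the planned effect is safe. About 9 per arm (4.6%), all falling against VHA, would be needed to lose significance. These figures assume equal missingness in the arms and the planned 28% v 15% among observed patients. The effect on mortality cannot be quantified, because the article gives neither mortality rates nor the number of patients affected. The practical effect is probably small, but the correction is nearly free and the rule is worth correcting.

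**What to change.** 1. *Method of analysis*: remove the condition on a recorded primary outcome. Analyse each endpoint in all randomised patients, as allocated, who have data for that endpoint. For mortality, use the Kaplan-Meier estimates already planned, with censoring at last known status.
2. *Primary endpoint* or *Method of analysis*: state that a documented death by 24 h, or 10 or more documented red cell units by 24 h, settles the composite as failure even if the other component is incomplete.
3. *Sensitivity analyses*: apply the planned 100 imputations to any missing primary outcomes as well, add a best/worst-case check, and identify this as the sensitivity analysis promised for the primary endpoint. Report the number missing by arm.
4. *Sample size*: say what the 13% allowance covers, given that withdrawn patients are replaced.

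The cost is a few sentences and a little extra analysis. No new data are needed, and the sample size of 392 is unchanged.
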